#### Intervention protocol

Participants randomised to the intervention will be contacted by the swimming coaches leading the 8-session outdoor swimming course prior to the start and given further information and answer any questions. The outdoor swimming courses will be held in three sites in England. The course will run for 8 × 1 h sessions. During the course, participants will also continue with their usual care (medications and/or therapies). The groups will consist of only participants in the research study; the groups will not be open to the general public.

#### Course structure

The focus of these courses will be the safe enjoyment of the water rather than becoming an expert swimmer. The swim coach will phone or text participants the night before each session and meet them outside the facilities. They will walk into the facility together and will be shown where to change and what to bring with them to the water’s edge.

All swimmers will be supervised by the course staff (who have basic life support, lifeguard qualifications and have attended courses on mental health first aid and mental health awareness training), and they will only swim if it is safe to do so. It is not possible to offer a completely standardised course as local conditions will dictate what can be achieved in the sessions.

Outdoor swimming courses should be offered when the water temperatures are at their highest. Therefore, the intervention group will start their swimming course no earlier than the beginning of August and courses will finish no later than the middle of November. The sessions will include basic swimming skills (Lido only), safety, hazard awareness and risk assessment and development of competency to deal with moderate challenges when in the water, including floating and in-water-based skills. However, alternative arrangements and session plans will be available for adverse weather conditions that do not allow the swim to take place at the normal time.

Wetsuits will not be provided as the water will be between 15–20 °C), but participants can use their own wetsuit if they wish. It will be made clear to participants that they should leave the water immediately should they feel uncomfortably cold. Although the session is an hour in length, the maximum in-water time will be 30 min. The remaining 30 min will be split between the pre-swim briefing and post-swim rewarming. After exiting the water, participants will return to the changing areas and change into warm dry clothes. Participants will be encouraged to have a hot drink. Risk assessments will be carried out on the day by the swim coach and lifeguard. Participants will consent for the research team to provide the swim coaches with details of medical conditions, swim experience and emergency contact details. At all times, clients will be monitored closely for signs of hypothermia.

During the course, participants will be supported to find existing groups or form their own so that they can continue to swim safely after completion of the course.

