The water around the UK is cold all year, and therefore, open water swimming in the UK is considered cold water swimming. Typically, summer water temperatures are between 15 and 20 °C, and conversely, water temperatures can become very cold in winter between 0 and 7 °C [31]. As such, there is a seasonality to outdoor swimming, particularly for those being introduced to the activity, as it is recommended that they start in the summer months [32] when the water temperatures are at their highest. They can then choose to continue as the water cools. As participation in groups is strongly encouraged, for safety reasons, many groups will modify the activity reducing the time in the water during colder months; wear neoprene gloves, boots and a wetsuit in winter [32], and try different locations where the water temperature may be higher, and some may also decide not to swim but maintain contact with the group during this time. These are all potential mitigations to the seasonal nature of the activity. As the effect on depressive symptoms of such an intervention has not been investigated by a robust RCT, the potential mechanisms of the effect have also not been fully investigated; whilst outdoor swimming may be seasonal in the UK, it does not mean all outdoor swimming activity would stop.

Further trials using robust designs, including RCTs incorporating mixed methods, are required to understand if outdoor swimming has potential as a treatment for depression [33]. As outdoor swimming can also be hazardous [25], well-planned empirical research is needed to determine if it is safe and as helpful as early research suggests, before recommending it as an evidence-based treatment for depression. Likewise, it is essential to determine whether sufficient numbers of people with depression will be interested in participating in the intervention, who it most benefits and if it is less attractive to some members of the population and whether measures can be put in place to address this.

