#### Usual care protocol

The usual care only arm will act as the control. They will be treated in accordance with the current NHS care by their medical providers. During the study, they may be taking medications, be on waiting lists for engaging in talking therapies, or participating in other social prescribing activities. Their participation in other interventions will be variable and we will ask them to record any treatments or interventions they engage in. Participants randomised to this group will be given the opportunity to participate in an introductory course of outdoor swimming upon completion of the study to thank them for their participation. This was advised by PPI representatives as a way to increase the likelihood of participants agreeing to the randomisation process and reduce the number who may drop out. Funding for these courses has been secured.

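### The water temperature given as the reason for not providing wetsuits (15–20 °C) is the protocol's own summer range, but courses may run to mid-November and nothing in the article supports that range for autumn sessions

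*Protocol article*

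**What the plan says.** Three statements in the protocol article bear on this.

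- **Reason for the wetsuit provision (Course structure).** "Wetsuits will not be provided as the water will be between" 15–20 °C. The sentence names no month and no site. Participants may bring their own wetsuit.
- **Course dates (Course structure).** The section opens its reasoning with "Outdoor swimming courses should be offered when the water temperatures are at their highest" and concludes that "the intervention group will start their swimming course no earlier than the beginning of August" and that "courses will finish no later than the middle of November".
- **Seasonal temperatures (Background).** "Typically, summer water temperatures are between 15 and 20" °C, whereas "water temperatures can become very cold in winter between 0 and 7" °C. For people new to the activity, "it is recommended that they start in the summer months", which the same sentence identifies as the time of warmest water. It is then up to them whether to go on as the water cools.

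The courses take place in three kinds of water: sea, lake and an unheated lido (Participants). Recruitment was due to close on 6 September 2022 (Trial status). The number of sessions is eight; their frequency is not stated.

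**The concern.** A range that the Background describes as typical of summer reappears under Course structure as an unqualified statement about the water in which every course will be held. The permitted dates extend well beyond summer, and the Background itself says the water cools afterwards. The article does not explain why the summer range should hold in October or November, or why it should hold equally in sea, lake and lido.

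Two things are at stake. First, the temperature is the only reason given for a provision that affects participants. If it does not hold for later sessions, the provision has no stated basis there. Second, the Background lists physiological responses to cold water among the possible mechanisms, so temperature is part of the exposure. A feasibility trial is meant to hand a describable intervention to the definitive trial. If the stated temperature is wrong for some sessions, the description passed on is wrong too.

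**Working it through.** The documents contain no temperature calculation to reproduce, so the check sets the statements side by side and adds calendar arithmetic.

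**Comparison**

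| Item | Background | Course structure |
|---|---|---|
| 15–20 °C | Typical of summer | Stated for the courses without limit |
| Winter | 0–7 °C | Not mentioned |
| Autumn | No figure | Sessions permitted to mid-November |
| Warmest water | The summer months | Given as the basis for a window from August to mid-November |

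The Course structure sentence is firmer than its counterpart: what is typical in the Background has become certain. The phrase about warmest water is also stretched, from the summer months to a window ending in mid-November.

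**How much of the window lies after summer**

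Assumptions: the year is 2022 (Trial status), the beginning of August is 1 August, and mid-November is 15 November.

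- Window length: 31 + 30 + 31 + 15 = 107 days.
- Summer ending 31 August: 30 + 31 + 15 = 76 days remain; 76/107 = 71%.
- Summer ending 22 September: 8 + 31 + 15 = 54 days remain; 54/107 = 50%.

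**Which courses are affected**

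Further assumption: weekly sessions, so that last session = first session + 7 weeks.

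| First session | Last session | Sessions after 31 August | Sessions after 22 September |
|---|---|---|---|
| 1 August (earliest allowed) | 19 September | 3 of 8 | 0 of 8 |
| 6 September (recruitment closes) | 25 October | 8 of 8 | 5 of 8 |
| 27 September (latest start that ends by 15 November) | 15 November | 8 of 8 | 8 of 8 |

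The first row fits the stated range if summer is taken to last to 22 September. The second row does not, on either definition. The third row is the outer limit, not a planned course.

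**What can be said about autumn temperature**

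Only an illustration is possible. Suppose a straight-line fall from the summer range (ending 31 August or 22 September) to the winter range (reached between 1 December and 1 February). On 15 November:

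- Coolest case, 15 °C on 31 August to 0 °C on 1 December: 15 − 15 × 76/92 = 2.6 °C.
- Warmest case, 20 °C on 22 September to 7 °C on 1 February: 20 − 13 × 54/132 = 14.7 °C.

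On 25 October, the warmest case gives 20 − 13 × 33/132 = 16.75 °C, which is still inside 15–20 °C. The straight line and its dates are assumptions, so this does not show what the water would be. It shows that the protocol's own figures do not secure the stated range late in the window.

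**The case against.** The strongest reply is that no contradiction is proved. Calling a range typical of summer does not say that the water leaves it when summer ends, and the article gives no October or November figure. That is right, and it limits the claim: the range is unsupported for autumn, not shown to be false. A reader might infer that late sessions would certainly be below 15 °C; the documents do not establish that.

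Second, mid-November is a latest finish, not a schedule. A start on 27 September would need a three-week gap after recruitment closes, which no section plans, and the provision for alternative arrangements in bad weather may explain some of the slack. This also stands. It does not remove the problem, because a weekly course starting on the day recruitment closes would still have most or all of its sessions after summer.

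Third, a reader might infer that the safety arrangements as a whole rest on 15–20 °C. They do not. The temperature is the reason for one thing, not supplying wetsuits. Course structure separately allows participants' own wetsuits, makes swimming conditional on its being safe, requires a risk assessment on the day, caps time in the water at 30 minutes, tells participants to leave if uncomfortably cold, and provides for rewarming and hypothermia monitoring. These lessen the consequence but leave the temperature statement uncorrected.

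Fourth, a reader might add that the control arm's "introductory course of outdoor swimming upon completion of the study" would fall in January, eight weeks after a mid-November finish. The Usual care protocol section gives neither a date nor a temperature for that course, and completion of the study does not fix it at that point. The inference is not supported and forms no part of this point.

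Finally, the article concedes that courses cannot be fully standardised and calls the trial pragmatic. That covers variation in what is done in a session. It does not justify one stated temperature range that may not apply to every session.

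**Conclusion.** The point holds in a limited form. The article states 15–20 °C without qualification as the reason for not providing wetsuits, describes the same range elsewhere as typical of summer, and permits sessions to mid-November without any support for that range in autumn. Between 50% and 71% of the permitted window lies after summer, depending on whether summer ends on 22 September or 31 August. The conclusion is inferred from the protocol's own seasonal ranges. The session counts rest on an assumed weekly schedule, but the mismatch between range and window does not.

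No estimate, sample size or progression criterion depends on this figure. It matters for the basis of one participant provision and for an accurate description of the exposure. It should be corrected, and doing so is cheap.

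**What to change.** 1. Reconcile the temperature statement under Course structure with the course window in the same section and with the seasonal ranges in the Background, for the dates and sites actually used.
2. Have the clinical and coaching team confirm the wetsuit provision that rests on it. What that provision should be is for them to decide.
3. Record water temperature at each session on a coach form and report it by site and date, so that a definitive trial inherits a correct description of what was delivered.

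The cost is a wording change, one confirmation by the team and a small recording task. The planned coach logs (Health economic measures) are designed for time and other resource use, so temperature needs a new item or a separate short form.

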#### Usual care protocol

The usual care only arm will act as the control. They will be treated in accordance with the current NHS care by their medical providers. During the study, they may be taking medications, be on waiting lists for engaging in talking therapies, or participating in other social prescribing activities. Their participation in other interventions will be variable and we will ask them to record any treatments or interventions they engage in. Participants randomised to this group will be given the opportunity to participate in an introductory course of outdoor swimming upon completion of the study to thank them for their participation. This was advised by PPI representatives as a way to increase the likelihood of participants agreeing to the randomisation process and reduce the number who may drop out. Funding for these courses has been secured.

### Intervention adherence and acceptability

Intervention adherence and acceptability will be assessed on the basis of attendance of participants at the swim sessions and rates of survey completions. Further information about the acceptability of the intervention and study design for participants will be gathered through the following: the evaluation forms and interviews with any participants who did not complete the intervention, from evaluation forms, focus groups and interviews with participants who completed the intervention or were in the control group, and from a focus group with the swim coaches.

### Serious adverse event monitoring

A protocol for identifying and independently assessing serious adverse events will ensure that such events are addressed in a timely fashion and responded to, including if a serious adverse event is classified as potentially study related. Serious adverse events and their classification will be reported to the Trial Steering Committee (TSC), and action will be taken as deemed necessary. Where deemed in the best interests of participants, the study intervention may be discontinued.

### Planned data analysis

Participant flow will be presented using a CONSORT diagram [57, 58]. Summary statistics (means, standard deviations, median, interquartile range, counts or percentages) will be provided for all demographics (age, gender, ethnicity, sexual orientation, disability status, religion or belief, relationship status, employment status and level of swimming ability), quantitative outcomes and feasibility measures.

Outcome, potential mechanism and health economic measures will be summarised for each trial arm at each time point. Effect sizes for between-group mean differences for each individual outcome and potential mediator measure will be estimated using linear mixed models post intervention (T1) and at 8-week follow-up (T2). The models will include fixed effects for treatment group (outdoor swimming + usual care, usual care), time (T1, T2) and the group × time interaction, the stratification variable (site) and the measure’s baseline score will be entered as covariates to adjust for potential bias and improve efficiency [59] and random effects will be added to account for repeated measurements on individuals. Parameter estimates with 95% confidence intervals will be presented, and there will be no hypothesis testing.

For PHQ-9 scores, 95% confidence intervals for the between-group difference will be reviewed with respect to the minimal clinically important difference (MCID) based on Kounali et al.’s [60] threshold of 1.7 for the difference between feeling better and feeling the same. We will proceed to a full trial if the 95% confidence interval for the between-group difference includes an effect in favour of the intervention arm of 1.7 PHQ-9 points at post-intervention, if the other feasibility parameters are met.

With regard to the economic outcomes, for the two economic measures of HRQoL, i.e. the EQ-5D-5L [48] and the ReQoL-10 [50], utility scores will be calculated using validated algorithms [49, 51, 61, 62] for the treatment and the control groups to explore which measure is more sensitive to changes over time. The use of all resources/services will be reported by trial arm, stratified by use/service type, as the mean, standard deviation, range and the percentage of the sample for each arm that had at least one contact/use, as applicable. Statistical analyses will be conducted using Stata version 16 (StataCorp), whilst Stata version 17 will be used for the health economics analyses.

Suitability and acceptability of the outcome, potential mechanism and health economic measures for a fully powered trial will be assessed based on measurement completion rates and participant’s feedback gained from evaluation forms, focus groups and interviews. Study findings will inform the selection of the primary outcome and inform the sample size of a future full-scale RCT should this study be deemed feasible.

Qualitative data will be analysed to identify facilitators and barriers to engagement with the study and with the intervention which will highlight areas that could be changed to improve acceptability in a full trial.

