**Fig. 1 Fig1:**
[figure not shown]
Schedule of enrolment, interventions and assessments

The sample size was based up on Teare et al.’s recommendation for pilot studies [34], where a total of 35 participants would be required per arm. To account for 20% drop-out, a total of 88 participants will be required. This drop-out rate is an estimate based on our previous single-arm study [28].

Evaluation questionnaires, semi-structured focus groups and interviews will be conducted with participants from both arms (at T2) to gain further understanding of barriers and facilitators to recruitment and retention in the study and, for those in the swimming arm, the barriers and facilitators to the swimming courses. Anyone who chooses not to participate will also be invited to complete a questionnaire and, if they had been consented to the study, attend an interview. In addition, social prescribers referring potential participants and the swim coaches providing the courses will be invited to attend focus groups to share their perspectives.

The study design was informed in consultation with a public and patient involvement (PPI) group and supported by the PPI co-applicant (SC). Members of the PPI group had previously participated in introductory swim courses, set up introductory swim courses for people with mental health difficulties or had lived experience of depression. The PPI group were instrumental in guiding the study team to focus on the participants’ journey through the trial, developing the participant information sheets and helping to inform the recruitment strategy.

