#### Multiple testing

As this feasibility study is exploratory and there is no hypothesis testing, there will be no adjustment made to the analysis for multiple testing.

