### Criteria for success

This feasibility trial, if successful, will inform the development of a full-scale RCT. Criteria for success of the feasibility work will include the following:• 80% trial retention at T1 for the PHQ-9• 80% attending four or more swim sessions• 80% data completeness• Collection of data on the experience of participation from at least 20% of participants• Findings indicate that taking part in this study was a positive experience for participants, link workers and coaches.

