The results of the feasibility RCT will be used to develop a protocol for a definitive full-scale RCT, which will be undertaken providing feasibility aims are met, or if not met could be addressed. The results of the full-scale definitive RCT will provide evidence regarding the clinical and cost effectiveness of open water swimming for depression. In addition, this potential future trial would explore the mechanisms involved in terms of “what provision works, and for whom?” as discussed by Garside [33]. As well as supporting the expansion of the range of nature-based socially prescribed activities, this would ensure that such interventions are targeting mechanisms of action as specifically as possible. Ultimately, we hope that this feasibility study will pave the way to develop the evidence base for open water swimming for depression, so that people living with depression may potentially have a greater range of options to support their recovery.

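### The PHQ-9 progression criterion requires the 95% CI to contain the single value 1.7, so an interval wholly above 1.7 fails it and a true benefit above 3.4 points meets it less often than no benefit

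*Protocol article*

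**What the plan says.** Planned data analysis sets the reference value at a "threshold of 1.7 for the difference between feeling better and feeling the same" on the PHQ-9 and treats it as the minimal clinically important difference (MCID). Its condition for going on to a definitive trial reads: "95% confidence interval for the between-group difference includes an effect in favour of the intervention arm of 1.7 PHQ-9 points at post-intervention", subject to the remaining feasibility parameters. The same section states that "Parameter estimates with 95% confidence intervals will be presented, and there will be no hypothesis testing", and Multiple testing repeats the point: "As this feasibility study is exploratory and there is no hypothesis testing". The interval criterion is therefore the only place where an estimated effect feeds a decision.

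Criteria for success gives the other parameters, including 80% retention at T1 for the PHQ-9, introduced by "Criteria for success of the feasibility work will include the following". The Discussion says of the definitive trial: "which will be undertaken providing feasibility aims are met, or if not met could be addressed". The sample-size paragraph under Design and sample size cites a recommendation "where a total of 35 participants would be required per arm". No PHQ-9 SD or expected interval width is given.

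**The concern.** A progression criterion based on effect should become easier to meet as the true benefit grows. This one asks whether the interval contains one particular value, with nothing to cover larger values. It can fail at either end: when the upper limit lies below 1.7, which is sensible, and when the lower limit lies above 1.7, which is the best result the study could produce.

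At stake is the decision on the definitive trial. Applied literally, a strong result fails the stated criterion, and the team must either follow it or reinterpret it once the estimate is known. Fixing a rule in advance is meant to avoid that choice.

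**Working it through.** **Scale.** Let d be the true between-group PHQ-9 difference at T1, with positive values favouring swimming.

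**Plan's own sample size.** 35 per arm gives 70. Allowing for 20% drop-out, 70/0.8 = 87.5, rounded up to 88, or 44 per arm. This matches the protocol, so 35 analysed per arm is the planned case.

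**The criterion in symbols.** With estimate e and half-width h, the interval contains 1.7 when e − h ≤ 1.7 ≤ e + h, that is, when |e − 1.7| ≤ h. An interval of 2.0 to 6.0 (e = 4, h = 2) has |4 − 1.7| = 2.3 > 2, so it fails. No assumption is needed for this.

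**Result that does not depend on the SD.** If e is normal around d with standard error SE, then

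P(met | d) = Φ((1.7 + h − d)/SE) − Φ((1.7 − h − d)/SE).

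This depends on d only through |d − 1.7| and falls as that distance grows. No effect lies 1.7 from the reference value, and so does d = 3.4. The two pass equally often, and any d above 3.4 passes less often than d = 0.

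**Size, under assumptions.** The SD and the baseline–outcome correlation r are assumed, because the protocol gives neither. The T1 contrast from the mixed model is approximated by a baseline-adjusted comparison of means.

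- SE = SD × √(1 − r²) × √(2/35). With SD 5 and r 0.5: 5 × 0.866 × 0.239 = 1.035.
- h = t(0.975, 65) × SE = 1.997 × 1.035 = 2.07.
- Passing estimates: 1.7 ± 2.07, that is −0.37 to 3.77.
- d = 0: Φ(3.64) − Φ(−0.36) = 64%.
- d = 1.7: Φ(2.00) − Φ(−2.00) = 95%.
- d = 4: Φ(−0.23) − Φ(−4.22) = 41%.
- d = 5: Φ(−1.19) − Φ(−5.19) = 12%.

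| Assumed SD, r | Passing estimates | Met at d = 0 | Met at d = 5 |
|---|---|---|---|
| 4, 0.5 | 0.05 to 3.35 | 48% | 2% |
| 5, 0.5 | −0.37 to 3.77 | 64% | 12% |
| 6, 0.3 | −1.03 to 4.43 | 77% | 34% |

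The first and last rows are the extremes over SD 4 to 6 and r 0.3 to 0.5.

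**Smaller SDs.** A separate calculation used the baseline-adjusted SD directly, with 68 degrees of freedom. At an adjusted SD of 3 the pass rate at no effect is 35%. It reaches 50% at an adjusted SD of about 3.56. A simulation with estimated SDs agreed to within about one percentage point.

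**Effect of an upper-limit rule.** If the criterion is e + h ≥ 1.7, then P(met | d) = 1 − Φ((1.7 − h − d)/SE). With SD 5 and r 0.5 this is 64% at d = 0, 98% at 1.7, and above 99.9% at 4 and 5.

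**The case against.** The strongest reply is that the sentence is loose, not wrong. It says the team will proceed if the condition holds, not only if it holds. It follows a statement that intervals will be reviewed against the MCID, and the natural intention is that an MCID-sized benefit has not been ruled out. The Discussion also allows unmet aims to be addressed. This stands in part: a reader might infer that a very good result stops the programme, and the documents do not say that. What they do is state a criterion that such a result fails and give no instruction for it. The probable intention is a different rule from the one written.

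The literal rule also does little harm near the MCID. With SD 5 and r 0.5, a true benefit of 2.5 passes 89% of the time and 3.0 passes 77%. The inversion relative to no effect begins only beyond 3.4, twice the MCID.

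Three stronger readings are tempting and are not supported:

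- **That the rule usually lets an ineffective intervention through.** This depends on an SD the protocol does not give: 35% at an adjusted SD of 3, 48–77% over the range above. It is also the pass rate for one criterion among several. Some leniency is normal in an exploratory feasibility study.
- **That heavy drop-out makes progression easier.** A wider interval does contain 1.7 more often, but the other feasibility parameters must also be met. Twenty analysed of 44 per arm is 45% retention, which fails the 80% criterion.
- **That the three statements of the decision contradict each other.** The success list is introduced as what the criteria will include, so it need not be exhaustive. The analysis section refers to other parameters, and the Discussion is compatible with both.

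**Conclusion.** The criterion is wrong as written. That an interval wholly above 1.7 does not meet it follows from the wording alone. That a true benefit above 3.4 points meets it less often than no benefit holds for any SD, given an approximately normal estimate whose precision does not depend on the effect. The percentages are illustrative: they rest on 35 analysed per arm and on assumed SDs of 4 to 6 and correlations of 0.3 to 0.5. They describe this criterion only, not the overall chance of a full trial, which also depends on the other parameters and on the judgement the Discussion allows. The pass rate at no effect is not itself the defect. It shows that meeting the criterion is not evidence of benefit.

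**What to change.** Reword the effect criterion so that it covers values of 1.7 or greater. For example: *the effect criterion is met when the upper limit of the 95% CI for the T1 PHQ-9 difference, taken in the direction of benefit, is at or above 1.7 points; the remaining feasibility parameters must also be met.* Add a sentence describing it as a screen that an MCID-sized benefit is not ruled out, not as evidence of benefit.

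This raises the pass rate at a true benefit of 4 to 5 points to about 100% and leaves the rate at no effect essentially unchanged (64% with SD 5 and r 0.5). Also requiring the point estimate to favour swimming would hold the rate at no effect to at most 50%. It has a price: with SD 6 and r 0.3, the pass rate at a true effect of 1.7 falls to 89%, against 98% for the upper limit alone. That is an optional trade-off, as is publishing the pass probability under no effect.

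The cost is one or two sentences in the protocol or analysis plan and no new data. The change should be made before results by arm are seen.
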